## Abstract

**Background:**

Nature exposure has been associated with mental health and cognitive benefits among older adults. However, controlled trials evaluating specific types of nature-based interventions are limited. This study aims to examine the effects of two structured outdoor activities, walking with meaningful conversation and group meditation, on mental vitality and cognitive empowerment in elderly women.

**Methods:**

This is a three-arm parallel randomized controlled trial (RCT) enrolling 111 women aged ≥ 60 from 9 urban and rural health centers in Khafr County, Iran. Participants will be randomized into the following: (1) Walking with meaningful conversation group, (2) meditation in nature group, and (3) control group with no intervention. Each intervention consists of eight 2-h sessions across 8 weeks. Assessments will occur at baseline, post-intervention (week 8), and 3-month follow-up using validated questionnaires on mental vitality and cognitive empowerment. The generalized estimating equation (GEE) model will be applied to analyze changes over time.

**Discussion:**

We hypothesize that both intervention groups will show significant improvements compared to the control, with walking expected to yield greater gains in mental vitality and meditation to better enhance cognitive empowerment. Findings may support the implementation of community-based, non-pharmacological programs to promote active aging.

**Trial registration:**

Iranian Registry of Clinical Trials IRCT20241023063481N1. Registered on 18 February 2025.

**Supplementary Information:**

The online version contains supplementary material available at 10.1186/s13063-026-09549-y.

## Introduction

In recent decades, rapid lifestyle changes and increasing urbanization have led to a reduction in older adults’ interaction with natural environments [1]. Simultaneously, the rising prevalence of cognitive decline and mental health disorders in this age group poses a significant challenge to healthcare systems. This trend necessitates innovative interventions that not only prevent the deterioration of older adults’ mental and psychological functioning but also contribute to the enhancement of their cognitive abilities and the improvement of their quality of life [2]. One emerging area in this field is the utilization of nature therapy and nature-based activities, which have garnered attention as non-pharmacological and low-cost approaches [3].

Previous studies have indicated that exposure to natural environments can help reduce stress, improve mood, and enhance concentration. Attention restoration theory [4] posits that nature can alleviate mental fatigue and increase attentional capacity. Furthermore, research emphasizes that even passive observation of natural landscapes and spending time in green spaces can improve cognitive performance. However, most of these studies have focused on passive engagement with nature, encompassing general characteristics such as green space, natural light, and fresh air, with less investigation into the impact of different types of nature-based activities on cognitive and mental well-being [5–7].

Despite this evidence, it remains unclear whether all nature-based activities are equally effective or if the type of activity and the level of an individual’s cognitive, emotional, and social engagement with the environment play a role in its effectiveness. Some researchers have categorized nature-based activities from several perspectives: physical activities (such as walking, running, or yoga in nature), cognitive and mindfulness activities (such as meditation, breathing exercises, or mindful attention in nature), and social and interactive activities (such as meaningful conversations in natural settings or participation in nature therapy groups). From a cognitive standpoint, some of these activities, like walking combined with social interaction, may enhance executive function and working memory [8], while meditation and breathing exercises in nature may directly improve mood and reduce anxiety by lowering stress levels and increasing present moment awareness [9]. Moreover, the individual or group nature of the activities may also influence outcomes. For instance, some studies have shown that social activities in natural environments can increase feelings of connection and social support, leading to more positive effects on mental health [10]. Additionally, the biological mechanisms of these interventions may differ; motor activities in nature can contribute to improved cognitive function by increasing blood flow to the brain and reducing neuroinflammation [11], whereas mindfulness and meditation-based interventions in nature may activate neurotransmitter pathways related to stress reduction and increased neural plasticity [12].

Given these findings, the key question is whether the type of nature-based activity creates a significant difference in its effectiveness on the cognitive and mental health of older adults, and if so, which type of intervention is more effective and what is the nature of its impact? This issue represents a significant research gap, and its investigation could optimize nature therapy programs for older adults to aid in the design of cognitive decline prevention programs. This study aims to address it by primarily comparing two specific structured activities, walking with meaningful conversations and meditation in nature, with a focus on two key psychological outcomes: mental vitality, defined as the subjective experience of energy and aliveness [13], and cognitive empowerment, understood as the perceived capacity to adapt to and manage one’s cognitive engagement [14]. The results will subsequently be compared with a control group.

### Aims

To determine the relationship between cognitive empowerment and mental vitality in older adults participating in nature-based activitiesTo determine the sustainability of the effects of nature-based activities on cognitive empowerment and mental vitality over timeTo explore the association of demographic characteristics (age, occupation, education level, retirement status, marital status, number of children, perceived economic status, and living situation) with the effectiveness of nature-based activities on cognitive empowerment and mental vitalityTo explore the association of health status (number of medications used, history of chronic diseases, multimorbidities, uncorrected disability, history of hospitalization in the past year, perceived health status, and physical activity) with the effectiveness of nature-based activities on cognitive empowerment and mental vitality

### Hypothesis

This research is based on the premise that the type of nature-based activity will have differential effects on the cognitive empowerment and mental vitality of older adults. It is expected that walking accompanied by meaningful conversations will have a stronger impact on these outcomes through social interaction, cognitive stimulation, and the enhancement of a sense of meaning, while meditation in nature, by reducing stress, improving focus, and strengthening emotional regulation, may produce different yet significant effects. Furthermore, it is hypothesized that both interventions will lead to greater improvements in mental vitality and cognitive empowerment in older adults compared to the control group, which will not be exposed to any structured nature-based activities.

## Materials and methods

### Study design

This study is designed as a three-arm, parallel-group, randomized controlled trial (RCT) within a superiority framework. It aims to evaluate the superiority of two nature-based interventions, walking with meaningful conversations and group meditation in an open natural environment, over a no-intervention control condition, on cognitive empowerment and mental vitality in older women (Fig. 1). A multistage cluster sampling method will be used for participant recruitment. Eligible participants will be randomly assigned to one of the two intervention groups or a control group (Fig. 1). This study will be conducted in nine main phases: (1) Preparation phase: including obtaining ethical approvals, training, and coordinating the research team; (2) screening: the initial phase for identifying participants and recruiting volunteers; (3) informed consent: obtaining consent from participants for study enrollment; (4) randomization allocation: randomly assigning participants to the intervention and control groups; (5) baseline assessment (pretest): to measure cognitive empowerment and mental vitality; (6) conducting an intervention: participants in the intervention groups receiving the two intervention methods and the control group receiving routine health care; (7) post-intervention assessment (posttest): conducted immediately after the intervention to evaluate short-term effects; (8) follow-up phase: 3 months post-intervention to examine the long-term sustainability of the intervention effects; and (9) data analysis: data entry and statistical analysis, interpretation of results, and dissemination of findings.

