### Requirement

To recruit volunteers, a public and targeted call for participation will be disseminated throughout the nine urban and rural health service centers. This call will aim to inform potential participants about the study and the initial inclusion criteria, providing them with general information to facilitate informed decision-making regarding their participation, based on an understanding of the research objectives and involvement requirements. The call for participation will include details regarding the study title and purpose, general inclusion criteria, duration and format of participation, benefits and incentives for participating, and contact information for registration or further inquiries. This call will be disseminated through various informational methods, including the placement of posters, the organization of introductory meetings, and the distribution of informational messages from the urban and rural comprehensive health service centers.

Upon receiving expressions of interest in participating in the study, volunteers will be screened according to the inclusion criteria by initial interview to assess health history, balance test (Additional File 1), and a Mini-Cog test. Volunteers whose scores on these assessments fall within acceptable ranges will proceed to the next stage of the study. Following screening, comprehensive research information will be provided to eligible participants. This information will include detailed explanations of the study objectives, research methodology, participant commitments, the benefits of study participation, potential risks and limitations, and the right to withdraw from the study at any stage without any consequences. To ensure complete understanding among volunteers, all questions will be addressed.

The principal investigator obtained written informed consent from each participant in person. Following this, the same researcher conducted a face-to-face interview to collect baseline data, which included completing the cognitive empowerment and mental vitality questionnaires. This process will continue until the required sample size is achieved. In this way, all participants will enter the intervention simultaneously, since the study will be a group intervention.

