### Sampling method

A two-stage cluster sampling method will be used to ensure adequate sample representation. Khafr County comprises nine comprehensive health centers, including three urban and six rural centers. Additionally, the rural centers will be affiliated with 27 health posts, each responsible for providing services to local families. In the first stage, each urban and rural comprehensive health center will be considered an independent cluster. Three centers (one urban and two rural) will be randomly selected. In the second stage, sampling will be conducted from the population covered by the selected centers. In each rural center, two affiliated health posts will be randomly selected. Then, eligible participants will be randomly chosen from the registries of these health posts and the selected urban center. To maintain equal representation, 50% of participants will be selected from urban areas and 50% from rural areas.

After enrollment, participants will be assigned to one of three groups, walking, meditation, or control, using block randomization. Each block will consist of 6 individuals, with a total of 20 blocks stratified by setting: 10 urban and 10 rural. Allocation concealment will be ensured using sealed envelopes, and responsibilities will be separated so that the person enrolling participants will be different from the one assigning them to groups. Participants will be placed in blocks based on registration order. Each block’s group codes will be enclosed in a sealed envelope. Upon registration of each set of six participants, the envelope will be opened, and codes will be written on separate cards. The randomization coordinator will then be contacted to determine each participant’s group based on the assigned code. This process will be repeated for all participants. A third party using the 2022 version of the Sealed Envelope online tool, independent of both the enrolling staff and the intervention investigator, will perform randomization. To prevent information exchange between groups, the walking and meditation sessions will be scheduled at different times and supervised directly by the researcher.

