## Trial status

This protocol is version 1.0, dated June 27, 2025. Recruitment has not yet started. The anticipated start date for participant recruitment is 1 August 2025. The approximate date for completion of recruitment is expected to be 1 March 2026.

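### The protocol lists random allocation before the self-reported baseline in one section and implies the reverse in others, and never requires baseline to be complete before allocation is released

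*Protocol article*

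**What the plan says.** The Protocol article describes the order of baseline and allocation in several places.

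- **Study design** numbers the phases. Consent is phase 3, and then come "4) randomization allocation: randomly assigning participants to the intervention and control groups; (5) baseline assessment (pretest".
- **Requirement** describes written consent taken by the principal investigator, and then: "Following this, the same researcher conducted a face-to-face interview to collect baseline data". It adds that "This process will continue until the required sample size is achieved" and that "all participants will enter the intervention simultaneously".
- **Sampling method** states "After enrollment, participants will be assigned to one of three groups" and "Upon registration of each set of six participants, the envelope will be opened". It does not say whether registration includes a completed baseline questionnaire.
- **Pretest (baseline measurement)** asks only that the pretest come before the intervention.
- **Table 2** gives 2 weeks for recruitment, followed by a separate 1-month stage that holds both the pretest and the start of the interventions.
- **Trial status** gives a recruitment start of 1 August 2025, and "The approximate date for completion of recruitment is expected to be 1 March 2026".

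The text under Fig. 1 says that participants and group leaders will know the assignment and that the questionnaire results are unblinded. Primary outcome defines the endpoint as the change in cognitive empowerment score from baseline to week 8.

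**The concern.** The two orders cannot both hold, and the difference matters for this endpoint. A baseline score given before allocation cannot depend on the arm. One given after allocation can: a woman who has just learned that she is in the control group may answer differently from one who expects outings, and a face-to-face interviewer who knows the arm may influence the answers. Because the primary outcome subtracts the baseline, any such shift enters the treatment effect with its sign reversed.

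The same applies to other self-reported baseline items. Statistical methods selects covariates by their between-group differences at baseline and names physical activity as an example.

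The timing raises a lesser question. If baseline is taken at consent and all women start together, those who enrol early wait longest between baseline and first session.

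**Working it through.** **Order of events**

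| Section | Order given or implied |
|---|---|
| Study design | consent, allocation, baseline |
| Requirement | consent, then baseline; allocation not mentioned |
| Sampling method | enrolment, then allocation in blocks of six; baseline not mentioned |
| Pretest | baseline before intervention; allocation not mentioned |
| Table 2 | recruitment, then a stage with pretest and start of interventions; allocation not mentioned |

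Requirement and Sampling method together suggest baseline before allocation. Study design states the opposite. No section ties the opening of an envelope to completed baseline questionnaires.

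**Effect of a shift in baseline answers**

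Let s be the arm difference in baseline answers caused by knowing the arm (active minus control).

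- Difference in change scores, which is what a group-by-time contrast estimates at week 8: bias = −s. With s = 1 point, the bias is 1 point in size.
- Adjustment for baseline as a covariate: bias ≈ −ρ × s, where ρ is the correlation of baseline with week 8 and the variances are taken as equal. The protocol gives no ρ. For assumed values of 0.3, 0.5 and 0.7, the bias is 0.3, 0.5 and 0.7 points in size.

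The size of s is unknown. These figures show how a shift carries through, not how large it would be.

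**Wait between baseline and start**

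- Trial status dates: 1 August 2025 to 1 March 2026 is 212 days, or 212 / 30.44 = 7.0 months. This is the wait of a woman enrolled on the first day, if the sessions start when recruitment closes. Her interval from baseline to posttest would be 212 + 56 = 268 days, about 38 weeks. For the last woman enrolled it would be about 8 weeks. Under even accrual (an assumption), the mean wait would be 212 / 2 = 106 days.
- Table 2: 14 + 30 = 44 days at most, about 6 weeks.

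**Precision, as illustration only**

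With outcome variance σ², a change score has variance 2σ²(1 − ρ) and a baseline-adjusted score has σ²(1 − ρ²).

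| Assumed ρ | Change score | Ratio to ρ = 0.7 | Baseline-adjusted | Ratio to ρ = 0.7 |
|---|---|---|---|---|
| 0.7 | 0.60σ² | 1.00 | 0.51σ² | 1.00 |
| 0.6 | 0.80σ² | 1.33 | 0.64σ² | 1.25 |
| 0.5 | 1.00σ² | 1.67 | 0.75σ² | 1.47 |
| 0.3 | 1.40σ² | 2.33 | 0.91σ² | 1.78 |

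A fall from 0.7 to 0.5 would thus raise the two variances by 67% and 47%. None of these correlations comes from the protocol, and the table applies each one to every woman, although the waits would differ.

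**The case against.** The strongest reply is that the phase list is only an overview, while the procedural sections point to the safe order: consent, baseline interview, and then assignment once six women have registered. Sampling method also separates the person who enrols from the person who assigns and has a third party randomise. The SPIRIT schedule (Fig. 3) and the flow chart (Fig. 1) are not reproduced in the text at hand and may show the intended order.

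Much of this stands. The safe order is the more natural reading of the procedural sections, and a figure may support it. But a figure would not remove the opposite order from Study design, and separating roles protects concealment without fixing when the baseline is taken.

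A reader might infer more than the documents support, in three ways.

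- **That the baseline is unblinded.** The protocol does not say that arms are disclosed before the pretest. This is a risk if the phase list is followed. The idea that the interviewer knows the arm also combines the interviewer from Requirement with the order from Study design.
- **That the baseline is both unblinded and months old.** Knowledge of the arm follows from the Study design order. The long wait follows from baseline at consent, as in Requirement. They are alternative readings. The 7 months also rests on Trial status alone, applies only to the earliest women, and conflicts with Table 2.
- **That an old baseline biases the comparison.** If it is taken before allocation, randomisation balances it across arms in expectation. It costs precision and makes the interval to posttest uneven, but it does not favour an arm.

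**Conclusion.** The concern holds as an unreconciled order with one harmful reading. Study design puts allocation before a self-reported baseline, Requirement and Sampling method suggest the reverse, and no sentence settles the matter. If Study design is followed and women learn their arm before answering, a shift in baseline answers passes in full into the primary change score and, under baseline adjustment, in the proportion ρ. The amount cannot be estimated from the documents.

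The wait before the start is a secondary matter of precision: up to about 7 months on one timeline and about 6 weeks at most on the other. The 67% and 47% figures illustrate assumed correlations and are not a prediction for this trial.

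**What to change.** 1. In Study design, exchange phases 4 and 5 so that baseline precedes allocation.
2. In Sampling method, state that a block's envelope is opened only after all six women in that block have completed the baseline questionnaires. Check that Figs. 1 and 3 show the same order.
3. Reconcile the recruitment period in Table 2 (2 weeks) with that in Trial status (1 August 2025 to 1 March 2026).
4. Where feasible, take the pretest close to the first session and still before allocation.

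Items 1 to 3 are changes of wording and cost almost nothing, since Trial status says that recruitment has not started. Item 4 is optional and has a real cost. Envelopes could no longer be released block by block as women register, and women who consented early would have to be contacted again. A single 2-week window, for example, would mean 111 face-to-face interviews in about 10 working days, or roughly 11 a day for the one researcher whom the protocol assigns to this task. A longer window or a second trained interviewer would ease that load.

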**Fig. 1 Fig1:**
[figure not shown]
Study design algorithm: eligibility criteria, random allocation, and follow-up process

Given the active nature of the sessions, participants and those leading the groups will know their assignment. Outcome scores come directly from participant questionnaires, so those results are also unblinded. For the analysis phase, the statistician will work without knowing group labels until the final results are prepared.

### Sample size

The required sample size was calculated using G* Power software, based on the method described by Kazazi et al. [13]. Among the study objectives, the one requiring the largest sample was selected as the basis for estimation, specifically the evaluation of the intervention’s effect on cognitive empowerment in older adults. According to prior data, the mean (±standard deviation) of the mental status examination scores after the intervention was 28.3 ± 1.8 in the intervention group and 27.5 ± 2.1 in the control group. Using these values, the calculated effect size was 0.41. With a statistical power of 95% and an alpha level of 0.05, and assuming two repeated measurements after the intervention, the minimum required sample size was determined to be 58 participants. To account for a possible 20% attrition rate and a design effect of 1.6 due to cluster sampling, the final adjusted sample size was increased to 111 participants, resulting in 37 individuals per group.

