### Statistical methods

To assess the homogeneous distribution of confounding variables across the three groups before the intervention, the chi-square test was used for categorical variables, and one-way ANOVA was applied for continuous variables. All analyses will follow the intention-to-treat principle. Missing data (up to 14%) will be imputed using regression methods.

The primary analysis will test the superiority of the interventions on the primary outcome: change in cognitive empowerment score at week 8. To account for multiple comparisons, the significance level for the three pre-planned between-group comparisons (walking vs. control, meditation vs. control, walking vs. meditation) will be adjusted using the Bonferroni correction, resulting in a corrected alpha of 0.0167.

Changes in outcomes over time, between groups, and their interaction will be analyzed using the generalized estimating equation (GEE) model. Baseline individual and clinical variables showing significant between-group differences (e.g., age, marital status, physical activity) will be included as covariates to control for potential confounding. Analyses for secondary outcomes will be considered exploratory.

All analyses will be conducted using Stata version 17, with a two-tailed alpha level of 5% for tests not covered by the primary correction. Graphs will be generated using GraphPad Prism version 8.

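### The sample size covers only an intervention-versus-control difference at alpha 0.05, yet is said to rest on the most demanding objective; walking versus meditation, a primary comparison at 0.0167, has no stated difference or power

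*Protocol article*

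**What the plan says.** Protocol article, Sample size: "Among the study objectives, the one requiring the largest sample was selected as the basis for estimation", named there as the intervention's effect on cognitive empowerment. The inputs are mental status examination scores of "28.3 ± 1.8 in the intervention group and 27.5 ± 2.1 in the control group", from which the article derives a standardised difference of 0.41. It then sets power at 95% and alpha at 0.05, allows for two measurements after treatment, and arrives at a minimum of 58. Allowances for 20% attrition and a design effect of 1.6 bring this to 111, or 37 per arm.

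Protocol article, Introduction: the study addresses its research gap by "primarily comparing two specific structured activities, walking with meaningful conversations and meditation in nature"; the comparison with control follows afterwards.

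Protocol article, Hypothesis: the section opens with differential effects by type of activity, then adds that "both interventions will lead to greater improvements in mental vitality and cognitive empowerment in older adults compared to the control group".

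Protocol article, Study design: the superiority aim is both activities over a no-intervention control.

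Protocol article, Statistical methods: the primary outcome, change in cognitive empowerment at week 8, is tested in "three pre-planned between-group comparisons (walking vs. control, meditation vs. control, walking vs. meditation"), each at a Bonferroni level of 0.0167.

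**The concern.** The trial is sized on one contrast, while the Introduction leads with another. Walking versus meditation takes an equal share of the primary alpha, yet the article gives no expected difference and no power for it. The largest-sample sentence tells the reader that every other objective is at least as well covered. Across the three planned comparisons that does not follow, because two active arms that both beat control will usually differ from each other by less than the better one differs from control.

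Two things are at stake. A reader may take 95% power to apply to all three primary tests. And a non-significant walking-versus-meditation result, which is likely at modest gaps, could be taken to mean that the type of activity does not matter.

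**Working it through.** **Inputs from the protocol article.** Means and SDs 28.3 (1.8) and 27.5 (2.1); 95% power; sizing alpha 0.05; minimum 58; attrition 20%; design effect 1.6; 37 per arm; primary alpha 0.05/3 = 0.0167.

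**Assumptions.** Primary tests are two-sided. The walking-versus-meditation gap is not given, so a range is used. A baseline correlation r = 0.5 serves as an alternative to the unadjusted case.

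**1. The plan's own figures.**
- Effect size: 0.8 / √((1.8² + 2.1²)/2) = 0.8 / 1.956 = 0.409. This reproduces 0.41, an intervention-versus-control difference.
- Inflation: 58 × 1.6 × 1.2 = 111.4, so 111, and 111/3 = 37 per arm. This reproduces too.
- The 58 does not reproduce as a two-group comparison at d = 0.41. A two-sided t test at 0.05 with 95% power needs 156 per arm. About 58 appears only under software settings that the article does not state. That is a separate matter; the point here would remain if 58 were corrected.

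**2. Which comparison needs the larger sample.** Let the two effects against control be a and b, with 0 < b ≤ a ≤ 0.41. The active-active gap is a − b, which is below 0.41. Required n per arm is roughly proportional to 1/gap², so halving the gap roughly quadruples n. For 95% power at 0.05, unadjusted:
- gap 0.41: 156 per arm
- gap 0.205: 620 per arm

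Under these conditions the sized contrast is not the most demanding.

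**3. Power at the planned size and level.** Two-sample noncentral t, 37 per arm, df = 72, two-sided 0.0167, noncentrality (gap/√(1 − r²)) × √(37/2):

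| Gap (SD) | r = 0 | r = 0.5 |
|---|---|---|
| 0.41 | 25.3% | 34.6% |
| 0.205 (second arm has half of a 0.41 effect) | 6.4% | 8.2% |
| 0.1025 (second arm has three quarters) | 2.7% | 3.1% |

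These figures are before attrition. With 20% lost (37 × 0.8 = 29.6 per arm), power at a gap of 0.205 is 5.3% and 6.7%. The unadjusted gap detectable with 80% power at 37 per arm is about 0.75, nearly twice the planned effect against control.

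**4. The control comparisons.** The first row applies equally to walking versus control and meditation versus control at d = 0.41: 25% or 35%. At the 0.05 level used for sizing, the unadjusted figure is 41%. With only two confirmatory contrasts at 0.025 each, power at d = 0.41 would be 31% (r = 0) or 41% (r = 0.5).

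**The case against.** Several counter-arguments have force.

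- **The sentence may concern outcomes.** It could mean that cognitive empowerment needs more participants than mental vitality, and the Aims list contains no walking-versus-meditation objective. On that reading nothing here disproves it. It would still need rewording, because it does not say so, and no other statement tells the reader that one of the three primary comparisons was not sized.
- **The bound is conditional.** Effects of 0.60 and 0.19 both beat control and differ by 0.41. The 0.41 itself comes from a mental status score, so it fixes neither arm's effect on the trial's questionnaire.
- **Low power is not peculiar to this contrast.** At 0.41 the control comparisons fare no better.
- **The lead question is disputed within the article.** Study design makes superiority over control the aim. What the text supports is an inconsistency between the two sections.
- **Bonferroni over three pairwise tests is valid.** The Discussion also concedes that the sample size may limit power to detect group differences, though it does not single out this contrast.

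A reader might go further and infer that walking versus meditation has almost no power, that a null result will be misread, or that the contrast must lose primary status. The article does not support these. The 3% to 8% figures rest on assumed gaps. The plan is a superiority trial that sets no equivalence rule, so misreading is only a risk. And the Introduction and Hypothesis make differential effects a central premise, so demoting the contrast is a trade-off.

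**Conclusion.** The concern holds in a limited form. The calculation covers one intervention-versus-control difference at 0.05. The largest-sample statement does not hold across the planned primary comparisons if both activities beat control and neither effect exceeds 0.41. The stated 95% power does not describe any of the three tests as planned at 0.0167: under a two-sample comparison with 37 per arm and no attrition, power at 0.41 is 25% unadjusted or 35% with r = 0.5 for each of them. Walking versus meditation falls to 6% to 8% if its gap is 0.205. That gap and the correlation are assumptions; the documents give neither. The Introduction and Study design also disagree on which comparison leads.

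**What to change.** **Sample size.** Withdraw the largest-sample statement. Say that the calculation covers intervention versus control only. Restate power at 0.0167, with a range of assumed differences for walking versus meditation.

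**Statistical methods.** Replace plain Bonferroni with Holm, which keeps the family-wise error rate over the three comparisons and rejects everything that Bonferroni rejects, so no power is lost. Report walking versus meditation as an estimate with a confidence interval, and state that non-significance will not be read as equal effectiveness.

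**Introduction and Study design.** Reconcile which comparison leads.

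**Options for the sponsor, not required corrections.** One is to make walking versus meditation secondary and test the two control contrasts at 0.025 each. This raises their power at 0.41 from 25% to 31%, or from 35% to 41% with r = 0.5, but gives up a confirmatory test of a central premise. The other is to size the trial for a stated walking-versus-meditation difference, which would need far more participants: at a gap of 0.205, about 500 completers per arm for 80% power at 0.0167, unadjusted.

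The required changes cost wording and a recalculation, with no extra participants. Recruitment had not started at the protocol version date, so they can be made before data exist if that is still the case.
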